#### Pre-post epigenetic marker assessment

We will assess change from baseline to 10 weeks after the intervention in the polyepigenetic scores. Participants will provide an additional saliva sample (Oragene-DNA, DNA Genotek) during the same time as when they complete the pre-post EMA saliva samples mentioned above. DNA will be extracted from these saliva samples and DNA methylation will be measured using Illumina EPIC DNA methylation arrays and genome-wide SNP genotyping using Illumina Genome Screening arrays will be performed in all individuals not genotyped in Phase 1.

#### Pre-post inflammation marker assessment

We will assess change from baseline to 10 weeks after the intervention in CRP levels. Participants will provide an additional saliva sample during the same time as pre-test and post-test EMA assessment and epigenetic marker assessment mentioned above. CRP levels in the saliva will be extracted as markers of inflammation.

#### Weekly assessments during intervention

We will assess weekly changes in mechanistic variables of interest over the period of 10 weeks of intervention using the mobile or web app designed for the study. Participants will once a week complete CERQ, Perceived Stress Scale– 4-item version (PSS-4), FoC Scale (only following subscales will be assessed: Fear of Expressing Compassion for Others and Fear of Expressing Kindness and Compassion Towards Oneself), S-SCS (only following subscales will be assessed: Self-Kindness and Common Humanity), Mindfulness scale (CAMS-R [211] or FFMQ [212]), MAIA (only following subscales will be assessed: Self-Regulation and Body Listening), IRI (only subscale Personal Distress will be assessed), Penn State Worry Questionnaire-3 [213], Cognitive Control and Flexibility Questionnaire (CCFQ; [214]), Acceptance and Action Questionnaire (AAQ-II; [215]), Brief COPE, Inclusion of Other in the Self Scale (IOS Scale; [216]), stress assessment and stressor appraisal questions [209], and three self-generated questions on frequency and quality of social interaction and empathic listening.

#### Daily assessment pre and post daily intervention exercise

We will assess daily changes in mechanistic variables of interest over the period of 10 weeks of intervention using the mobile or web app designed for the study. Participants will be asked to evaluate their feeling of engagement with the exercise on a daily basis after the training session. Questions pre and post daily exercise sessions that will be presented alternately every other day include affective state (Affect Grid), valence, temporality and social orientation of thoughts (Cube of Thoughts), feeling of connectedness to partner (IOS), level of interoception (awareness of bodily sensations), and perceived loneliness. Level of personal detail shared (personal disclosure) will only be assessed after the Affect Dyad exercise in the socio-emotional intervention.

#### Phase 1 measures

Data on various measures of trait and state vulnerability, resilience, and social cohesion will also be obtained from the recently completed first phase of the CovSocial project (osf.io/jvb98). The data will be used to test hypotheses that predict impact of phase 1 trait and longitudinal assessments on intervention-related change in phase 2.

### Interventions

#### Socio-emotional mental training (group 1)

The behavioral intervention will consist of 10 weeks of daily Affect Dyad practice with a partner as the core exercise. In the Affect Dyad (AD), participants perform a 12-minute partner-based exercise which involves contemplating over the experience of one difficult situation and one situation which incurred gratitude in the past 24 hours. Both partners take turns speaking about the two situations while the other partner listens in a non-judgmental manner. While the participants elaborate on the situations, they are asked to mostly focus on the bodily experience of the emotions generated during the situation. Daily practice of the dyad begins with a moment of silence wherein participants are required to center themselves and let go of the events and feelings experienced during the day thus far. After this, the first partner speaks about a difficult or stressful situation they experienced during the past 24 hours, and the emotions arising in that situation were felt in their body. While the first partner speaks, the other partner remains silent and is instructed to listen in an empathic non-judgmental manner. After speaking for 2.5 minutes about the difficult situation, the first partner then speaks about a situation that made them feel grateful or gratitude experienced in the past 24 hours, and how the emotions arising during this situation were felt in their bodily sensations. The partner once again remains silent and listens with an empathic and non-judgmental stance. Once the first partner finishes speaking about the grateful situation for 2.5 minutes, the entire procedure is then repeated with the second partner as speaker and the first partner as listener. The exercise ends with a moment of silence once again. Participants perform this daily exercise 6 times a week. Prior to each week of daily dyad practice, the participants are randomly paired to one other participant in the Affect Dyad group. The goal of the exercise is to enhance coping with difficult emotions, increase social connectedness, (self) acceptance, empathic and non-judgmental listening and gratitude.

#### Mindfulness-based mental training (group 2)

The behavioral intervention will consist of 10 weeks of daily individual attention-based mindfulness meditation practice. One of the core practices will be Breathing Meditation (BM), a 12-minute individual exercise that requires participants to focus their attention on the sensations of breathing. Participants have to sustain their attention to breath for long stretches of time, and have to return their attention to their breath when their mind wanders. Participants will also engage in other practices, such as attention-based mindfulness on sounds (object of attention is sounds in the environment) and open presence meditation (object of attention is sensations present in the inner and outer environment). Daily practice of the meditation takes place through pre-recorded exercise audios recorded by meditation trainers who guide the participants through the entire 12-minute exercise. The exercise begins with participants being asked to sit in a comfortable position that makes them relaxed yet keeps them awake and aware. They are asked to feel the contact to all the objects that their body rests on, and are asked to cultivate an attitude of dignity and receptivity towards themselves and their body. The exercise encourages them to focus their attention on their breath, and to bring back their attention to the breath when their mind has become distracted or has wandered. The key focus of these practices is on training present-moment attention and interoceptive body awareness.

#### Retest control group (waitlist control group 3)

The retest control group, which is also a waitlist control group, will only be tested prior to and after the 10-week period at pre-test and post-test wherein other groups undergo the interventions. In a second step, the waitlist control group will then also undergo a 10-week period of socio-emotional intervention, with the exact same protocol as the socio-emotional intervention experimental group 1 described above.

### Instructor training

The interventions will be conducted using an online mobile and web app. However, participants will also be assigned to one of four MBSR-trained teachers. These instructors will introduce participants to the interventions, coach them on the basics of the interventions, and will conduct “weekly check-ins” with participants. All MBSR instructors have received a comprehensive in-house training, which includes multiple workshops by leading experts to ensure high qualification in their ability to manage participant adherence to the interventions.

### Procedure

The study will begin with the invitation of Berliners who took part in the first phase of the CovSocial project. The invitation for the current study will include brief information about the current second phase of the project, and the link to complete the online pre-screening questionnaire. Once interested individuals complete the prescreening, the results from the questionnaire will be analyzed to select the appropriate individuals who meet the inclusion and exclusion criteria (listed in the sample section above). The selected individuals will be randomly assigned to form three tentative groups with *n* = 200 each, socio-emotional intervention group, mindfulness-based intervention group, and retest control group (waitlist control). These selected individuals will then be invited to an online information webinar for further detailed information about the study, including introduction to the specific intervention they have been randomly assigned. Upon the webinars, individuals who express interest in taking part in the study will receive an email to formally sign up for the study by providing formal informed consent, in order to form final three *n* = 100 groups. The participants will then undergo short 30-minute screening calls with MBSR instructors, who will ultimately also track the progress of participants throughout the course of the intervention with weekly check-in meetings. After the screening calls, a final assessment of the three groups will take place, and further participants will be recruited in case of dropouts to make sure that we have *n* = 100 per group. This will complete the recruitment procedure which will take place entirely online.

After the recruitment, participants will complete a 2-week pre-intervention EMA, wherein they will provide saliva samples at specific timepoints and answer questions about their mental and physical health during those corresponding timepoints. This period of data collection will take place at the convenience of participants (at their home, workplace, etc.) to be able to capture the ecologically valid CAR and stress response. For this portion, participants will be sent the appropriate saliva collection kits by mail. Next, all participants will then be invited to the lab to complete the pre-intervention assessment of the behavioral tasks, and they will also complete the pre-intervention assessment of questionnaires using the web and mobile App. This pre-intervention assessment period will last approximately 4 weeks, after which the intervention period will begin.

The intervention period will last 10 weeks, and no blinding will be employed During each week participants in the two intervention groups will perform the intervention-specific exercises 6 times a week using the mobile or web app designed for the study. Every day prior to and after completing the intervention exercise, participants will complete the intervention-related daily EMA using app. Once a week, participants will undergo 2-hour online coaching sessions with an intervention instructor. The purpose of these so-called “weekly check-ins” would be to ensure that participants are able to share insights gained during the week, resolve issues faced during the week, and to keep up the motivation and commitment of participants. Once a week, at a random timepoint, participants will also complete the weekly assessment measures tracking changes in various potential mechanistic variables of interest using the app. During this first intervention period, participants in the retest control group will not complete any daily EMA or weekly assessments. After the completion of the first 10-week intervention period, all participants will again be invited to the lab to complete the same battery of behavioral tasks at post-intervention, and will also complete the same battery of questionnaires through the web and mobile App. Participants will once again undergo a 2-week post-intervention EMA period, during which they will provide saliva samples at specific timepoints, along with answering questions about mental and physical health at those timepoints.

Upon the completion of the post-test, all participants in the retest control group (waitlist control) will then undergo the 10-week socio-emotional intervention period. Same as above, during each week participants in the waitlist control group will perform the intervention-specific exercise 6 times a week. Every day prior to and after completing the intervention exercise, they will complete the intervention-related daily EMA, and once a week, they will undergo 2-hour coaching sessions with an intervention instructor. They will also complete the weekly assessment measures, once a week at a random timepoint, to track changes in various potential mechanistic variables of interest. The participants will then undergo post-test 2, wherein they will complete the behavioral tasks, pre-post questionnaires, and pre-post EMA. Lastly, post-test 2 will also be offered to participants in the other 2 groups depending upon the availability of resources.

Pre-post questionnaires will be assessed using an online survey which will be implemented in a research WebApp (app.covsocial.de). This WebApp has been developed for the purpose of the CovSocial project. The WebApp and linked Webpage (www.covsocial.de) are developed by the web agency CosmoCode GmbH. Weekly assessments during intervention and daily assessment pre and post daily intervention exercise will also take place through the app.

### Data management and monitoring

Data collection and management will adhere to German law. Participant data will be stored on encrypted institute servers in a pseudonymized manner. This will allow only the dedicated study personnel to access the full details of participants (i.e., personal identifying and study data). Since participants have the right to withdraw from the study at any time, provisions are in place to delete all individual data from servers if requested by a participant. Data will be presented in eventual publications, and will be fully anonymous. This anonymized dataset will be accessible to all investigators/authors of the protocol. Study documents will be kept at the Social Neuroscience Lab, Max Planck Society for the duration of the study and consecutive data analysis. Biological data will be stored in biobank. Since the current trial does not involve blinding, the establishment of a data monitoring committee is not necessary. The occurrence of adverse events will lead to the immediate exclusion of the participant from the study. These serious adverse events will be reported to the ethics commission of the Charité –Universitätsmedizin Berlin.

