
An estimated 300 individuals, 100 per intervention group, will be recruited. A priori effect size and power calculations have been performed based on the results from the previous mental training study, the ReSource project [67], which developed and validated the interventions being applied in the current study. Power analyses were conducted using G*Power [194] for analysis of variance with repeated measurements and interactions between group and intra-group variables. The analyses elements were as follows: an alpha level of .05, with a power (1-ß) of .80, 3 groups and 2 measurement occasions, a correlation of variables with repeated measurements of .39 which is the lower limit of retest reliability for the Cortisol Awakening Response (CAR; [195]), and an assumed small effect size of *f* = .10. This results in a total sample size of *n* = 297. For the additional third measurement time (post-test 2 following socio-emotional intervention given to waitlist control group) power analysis was conducted in a similar manner as above.

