#### Effects of mental training interventions on pre-post changes in variables of interest

In order to evaluate intervention-related effects on variables of interest, a mixed-effects modeling approach will be applied. Effects of time of assessment (pre-test/post-test for primary outcome variables and pre-training session/post-training session for secondary outcome variables respectively) and intervention group (socio-emotional mental training/mindfulness-based mental training/waitlist control group), as well as the interaction between time and group will be defined as fixed effects. Dummy coding with the waitlist control group as reference will be used for the intervention group variable. Additionally, we will control for participant-related random effects.

In addition, latent change scores for each primary outcome variable respectively will be computed with two timepoints (pre-test/post-test). The change in outcomes will be modeled as a latent variable and this latent change will be predicted by the treatment condition (path c in Fig 6). A correlation between the latent change score and initial levels on the primary outcome variable of interest is evaluated.

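### After an adverse event the participant leaves the whole study, not only the training, so later outcome data are lost; whether any event or only a serious one triggers this is unclear

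*Protocol article*

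**What the plan says.** Under Data management and monitoring, the rule is that "The occurrence of adverse events will lead to the immediate exclusion of the participant from the study". It continues: "These serious adverse events will be reported to the ethics commission". The first sentence gives no grade of severity, and the second calls the same events serious. Neither separates stopping the training from stopping the assessments, and no other part of the article keeps excluded participants in follow-up.

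The outcome schedule is short. Under Study design and setting, the two training groups have two planned assessments and the waitlist group has three. The main mixed model takes time as "pre-test/post-test for primary outcome variables", and the latent change score uses the same two occasions. For the waitlist group's own training period, the Procedure section says: "The participants will then undergo post-test 2, wherein they will complete the behavioral tasks, pre-post questionnaires, and pre-post EMA". The two training groups are offered post-test 2 only if resources allow.

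**The concern.** Protecting a participant after an adverse event may require that training stops. It does not require that the trial gives up the outcome measurement. With one planned assessment after baseline in the randomised comparison, exclusion before that assessment leaves only a pre-test value. The weekly and daily measures do not fill the gap. Trained participants supply them up to exclusion, but in the first period "participants in the retest control group will not complete any daily EMA or weekly assessments", so there is no control counterpart.

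Two things are at stake. The first is information: how people who had an event fared on the study's own outcomes, in a trial presented as a first step towards wide, low-cost use. The second is conditional. If exclusions differ between arms and excluded participants would have changed differently, the missing post-tests are informative and between-arm contrasts shift.

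The unclear trigger matters in its own right. If any adverse event counts, transient distress after an exercise could remove someone. If only serious events count, exclusions should be rare in this screened, non-clinical sample. Two members of staff could apply the same sentences differently.

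**Working it through.** **Step 1. What an exclusion costs, by timing.**

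| Event occurs | Planned data lost | Randomised contrast affected? |
|---|---|---|
| Before post-test, any arm | Post-test, the only post-baseline occasion in the main model | Yes |
| After post-test, training groups | None that is firmly planned (post-test 2 is optional for them) | No |
| Waitlist group's own training period | Post-test 2 | No, post-test is already collected |

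**Step 2. The plan's own sample size.** Inputs from the sample-size paragraph under Sample and sampling procedure: alpha 0.05, power 0.80, 3 groups, 2 occasions, f = 0.10 and "a correlation of variables with repeated measurements of .39". For the group-by-time interaction, lambda = f² × N × m / (1 − rho), with df1 = (3 − 1)(2 − 1) = 2 and df2 = N − 3.

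- At N = 297: lambda = 0.01 × 297 × 2 / 0.61 = 9.74, df2 = 294, power 0.8002. This is the smallest N that reaches 0.80, so the stated 297 reproduces exactly.
- At the planned N = 300: power 0.804. The margin is 3 participants, or 1%.

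**Step 3. Loss of precision.** The article gives no event rate, so the rates here are assumptions. Excluded participants are treated as contributing no change.

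| Excluded before post-test | N left | Power |
|---|---|---|
| 1% | 297 | 0.800 |
| 2% | 294 | 0.796 |
| 5% | 285 | 0.782 |
| 10% | 270 | 0.758 |

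**Step 4. Possible shift in a contrast between two arms.** Work in SD units of the outcome at one occasion.

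- SD of change = sqrt(2 × (1 − 0.39)) = sqrt(1.22) = 1.105.
- SE of a two-arm difference in change, 100 per arm = 1.105 × sqrt(2/100) = 0.156.
- Let p1 and p0 be the exclusion rates in the two arms, and let D be how much worse the excluded would have changed than those who remain. Comparing completers gives a shift of (p1 − p0) × D. D = 1 SD is an assumption.
- If the mixed model keeps participants who have only a pre-test, and exclusion depends on the change, part of the shift is recovered. The share remaining is (1 + 0.39)/2 = 0.695.
- Two-sided type I error = P(Z > 1.96 − shift/SE) + P(Z < −1.96 − shift/SE).

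| Assumed rates | Completer shift (SD) | Mixed-model shift (SD) | Mixed-model shift / SE | Type I error |
|---|---|---|---|---|
| Equal in both arms | 0 | 0 | 0 | 5.0% |
| 1% vs 0% (serious events only) | 0.010 | 0.007 | 0.04 | 5.0% |
| 5% vs 2% (any event) | 0.030 | 0.021 | 0.13 | 5.2% |
| 5% vs 0% (any event) | 0.050 | 0.035 | 0.22 | 5.6% |

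A simulation with 2,000,000 participants and logistic exclusion on the change gave mixed-model shifts of 0.0070 and 0.0351 SD at 1% and 5% versus 0%, in agreement with the formula.

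**The case against.** The strongest reply is that the two sentences, read together, describe serious events only: the participant leaves and the ethics commission is told. The sample is screened for psychiatric diagnosis, medication, chronic illness, high symptom scores and suicidality, and the exercises last 12 minutes a day. Serious events would probably be few. Ending all procedures after one is cautious, and it spares lab visits and a two-week saliva and momentary-assessment period. The detailed handling of events may also stand in the full protocol, which is not shown.

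Much of this stands, and it keeps the point small. It does not remove it, because the article states the rule itself, and states it as exclusion from the study. Even on the serious-only reading, outcome data after the event are lost.

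Four stronger readings are tempting, and the documents do not support them.

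- *The rule biases the trial in favour of training.* The trained arms have weekly sessions meant among other things to "resolve issues faced during the week", while the control group "will only be tested prior to and after the 10-week period at pre-test and post-test". A reader might infer that events are noticed more often under training. Neither those sessions nor the daily app items are described as collecting adverse events, so differential detection is conjecture.
- *The comparison of socio-emotional with mindfulness training is safe because contact is alike.* Similar contact bears only on detection. One group recounts a difficult situation to a partner each day and the other meditates alone, so event rates could differ by content.
- *Follow-up of the participant's safety ends.* The article does not say that care or monitoring of the event stops. What is lost is the trial's own outcome assessment.
- *Every exclusion costs the only follow-up value.* That is true only for an event before post-test.

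**Conclusion.** The point holds as a minor one. The rule ends assessment together with training, and its trigger is described in two ways. Outcome data after the event are lost if the event precedes post-test or, in the waitlist group's training period, post-test 2.

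The frequency of that loss is unknown. Any effect on between-arm contrasts depends on exclusion rates that differ and on excluded participants who differ in outcome. It is zero if either condition fails. Even the most unfavourable of the assumed scenarios moves the estimate by less than a quarter of its standard error. The case for change rests mainly on keeping outcome data on people who had an event, and on a rule that staff can apply consistently. The sample-size figure itself is correct.

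**What to change.** In Data management and monitoring, replace exclusion from the study with wording to this effect: *after the event, training is stopped where clinically needed; the post-test (or post-test 2 during the waitlist group's training period) is still offered if the participant agrees; and the participant stays in the analysis.* Use one term for the trigger, either adverse event or serious adverse event, in both sentences.

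The cost is two sentences of protocol text and a notification to the ethics commission, to which protocol modifications are already reported. The downside is a few additional assessments with people who have stopped training, all of them voluntary.
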